## Abstract

**Background:**

Childhood malnutrition is a crucial public health issue in developing countries. Mothers’ nutritional knowledge significantly affects children’s nutritional status. It also appears that mothers with low health literacy are unable to adequately meet their children’s nutritional needs because they do not clearly understand their children’s nutrition and malnutrition status.

**Methods:**

This randomized controlled trial aims to describe the development and study protocol of the *MyKid’sNutrition* application, a smartphone-based intervention for mothers of preschool (2–6 years old) children. The application contains several contents on children’s healthy eating, childhood underweight, children’s loss of appetite, and child growth assessment. As part of the *MyKid’sNutrition* trial, a total of 116 participants will be randomized 1:1 either to (a) treatment as usual and *MyKid’sNutrition* or (b) treatment as usual alone. The results of this trial will be based on changes in growth indicators and mothers’ nutritional knowledge, attitude, and practice within the groups and the differences between them.

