## Introduction

### Background and rationale {6a}

In developing countries, childhood malnutrition continues to be a significant public health and development issue, and inequities in malnutrition persist [1]. Studies demonstrated that undernutrition during childhood has considerable economic consequences regarding children’s health and development, including restricted growth, diminished intelligence, weak cognitive development, and reduced productivity when they become adults [2, 3]. Numerous diseases are associated with malnutrition on a global scale, and undernutrition is responsible for about half of the annual deaths of children under 5 worldwide. In 2020, the World Health Organization (WHO) estimated that 149 million children under 5 were stunted, and 45 million were wasted [4].

Three commonly known indicators of a child’s nutritional state are stunting (low height for age), wasting (low weight for height), and being underweight (low weight for age). While underweight is a compound index encompassing acute and chronic malnutrition, stunting and wasting indicate chronic and acute malnutrition, respectively. However, different types of malnutrition can develop concomitantly in children [5]. Primary indicators of undernutrition-related malnutrition in cases where only one data point is available for diagnosis are as follows: weight for height or body mass index (BMI) for age *z*-scores of − 1 to − 1.9 corresponds to mild malnutrition, − 2 to − 2.9 to moderate malnutrition, and below − 3 indicates severe malnutrition [6]. In addition to food security, the poor nutritional status of a child can also be attributed to access to health services, poor feeding practices in a community, nutritional knowledge and awareness, and quantity and frequency of the consumed food [7, 8].

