#### Eligibility criteria {10}

The inclusion criteria will be as follows: children aged 2–6 years at baseline; mothers’ willingness to participate in the study and signing a written consent form; having a smartphone and willingness to use a smartphone application; mothers’ reading and writing skills; and confirmed malnutrition and underweight using growth charts.

There will be two exclusion criteria as follows: subjects suffering from a specific disease that can affect the results and those reluctant to continue participation in the study.

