#### Intervention description {11a}

After recruitment into the study, the subjects will be randomized into two separate arms. The participants in the intervention group will receive *MyKid’sNutrition* application, which will provide educational contents on children’s nutrition and weight status. The duration of the intervention will be three months in total. Both groups will receive standard care, which consists of treatment as usual for undernutrition.

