#### Outcomes {12}

The outcomes of *MyKid’sNutrition* trial would be the change in the growth indicators and mothers’ nutritional knowledge, attitude and practice within the groups, and the differences between the groups. Weight for height and BMI for age *z*-scores, which are the growth indicators and mothers’ nutritional literacy, will be measured at baseline and after 3-month follow-up visits. Additionally, the participants’ demographic and socio-economic status will be measured.

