### Statistical methods

#### Statistical methods for primary and secondary outcomes {20a}

We will use descriptive statistics for summarizing and determining the sample’s characteristics and distribution among the patients. Frequencies and proportions will be used to summarize categorical data. Analyzing associations between qualitative data variables will be done using the chi-square (*χ*^2^) test or Fisher’s exact test, as appropriate. The unpaired *t*-test or Mann–Whitney *U* test will be used to analyze quantitative data between the two independent groups. The analyses will be adjusted for age, sex, and other baseline characteristics as covariates when needed. A 95% confidence interval will be provided for all comparative analyses, and statistical significance for main effects will be determined as 5%.

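### Within-group change stands unranked beside the between-group difference as a basis for the results, so a rise shared by both arms could be misread as an app effect

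*Protocol article*

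**What the plan says.** Two places in the protocol article state what the results rest on.

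- The abstract (Methods) names changes in growth indicators and in mothers' knowledge, "attitude, and practice within the groups and the differences between them".
- Outcomes {12} repeats this, ending with "attitude and practice within the groups, and the differences between the groups".

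Neither place gives one basis priority over the other.

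Four other sections bear on how a within-group change can be read.

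- Eligibility criteria {10} requires "confirmed malnutrition and underweight using growth charts", so children are selected on low anthropometric values.
- Outcomes {12} takes the growth outcomes from the same family of measures, "Weight for height and BMI for age" z-scores, which "will be measured at baseline and after 3-month follow-up visits".
- Intervention description {11a} says: "Both groups will receive standard care, which consists of treatment as usual for undernutrition".
- Statistical methods {20a} names an unpaired t-test or a Mann-Whitney test, which "will be used to analyze quantitative data between the two independent groups". It names no paired or within-arm test, and it leaves covariate adjustment optional.

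**The concern.** The objective is the effectiveness of the app, and the design is a 1:1 randomised comparison with usual care. Only the contrast between arms answers that question. A change from baseline within the app arm mixes any app effect with everything else that moves the outcome over three months.

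Here those other influences are expected to be real. Children chosen for low growth indicators will on average measure somewhat higher the next time (regression to the mean), and both arms are treated for undernutrition. Mothers are not selected on their knowledge, attitude or practice scores, so regression from selection does not apply to those. Usual care, the passage of time and answering the same questionnaire twice can still raise them in both arms.

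Because the outcome wording ranks neither basis, a report could set a null between-group result beside a marked improvement in the app arm and present the second as a finding on effectiveness. Nothing in the stated basis for the results would rule that out.

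**Working it through.** **The plan's own figure.** Sample size {14} gives 51 per group (102 in total) for alpha 0.05, power 0.80 and effect size 0.5. A two-sample t-test with these inputs needs exactly 51 per group if one-sided (power 0.806) and 64 per group if two-sided. A paired test would need only 27 or 34 children. The trial was therefore sized on the between-group contrast. The unstated sidedness is a separate matter. The figure of 51 per arm is used below.

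**Illustration: what a within-arm test would show if neither the app nor usual care did anything.**

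Assumed inputs, none fixed by the plan for this purpose:

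- Entry at z < -1. Background {6a} says a z-score of -1 to -1.9 "corresponds to mild malnutrition"; the eligibility section gives no numeric cut-off.
- Source population z-scores with mean 0 and SD 1.
- Correlation r between baseline and 3 months of 0.80 to 0.95.
- The measurement used for selection is also the baseline outcome.
- Two-sided 5% tests.

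Steps:

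1. Baseline after selection: L = φ(-1)/Φ(-1) = 1.525, so the mean z is -1.525. The variance is 1 + L - L² = 1 + 1.525 - 2.326 = 0.199.
2. Mean rise from regression alone: (1 - r) × 1.525.
3. SD of change: √[(1 - r²) + (1 - r)² × 0.199].
4. Chance that a paired t-test in 51 children is significant: noncentral t with 50 degrees of freedom and noncentrality (rise/SD) × √51.

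| r | Rise in z | SD of change | Rise/SD | P(significant) |
|---|---|---|---|---|
| 0.80 | 0.305 | 0.607 | 0.503 | 0.941 |
| 0.90 | 0.153 | 0.438 | 0.348 | 0.684 |
| 0.95 | 0.076 | 0.313 | 0.244 | 0.400 |

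**Sensitivity to the assumptions.**

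- With entry at z < -2, the rise is 0.475 to 0.119 and the chance is 100% to 76%.
- With a population mean of -0.5, the chance runs from 25% (entry at -1, r = 0.95) to 99% (entry at -2, r = 0.80).
- A usual-care gain of 0.1 z shared by both arms (population mean 0) lifts the chance to at least 97% in every scenario run.

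**The between-arm test under the same conditions.** Simulation with 10,000 runs per scenario (population mean 0; two cut-offs, three correlations, shared gains of 0, 0.1 and 0.2 z) gives a rejection rate of 0.045 to 0.055 for the unpaired test of change. Regression and usual care cancel between arms.

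**The pattern of app arm significant and control arm not.** With no effect of either treatment its probability is p(1 - p):

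- r = 0.80: 0.941 × 0.059 = 0.056
- r = 0.90: 0.684 × 0.316 = 0.216
- r = 0.95: 0.400 × 0.600 = 0.240

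The reference with no regression at all is 0.05 × 0.95 = 0.0475. The pattern is thus hardly more common than that reference when regression is strongest, and most misleading in the middle of the range, where p is near 0.5.

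**The case against.** The strongest reply is that the statistical section already does the right thing. It names only between-group tests for quantitative data, the sample size is a two-sample calculation, and the concurrent control arm regresses and is treated in the same way. The outcome sentences can be read innocently: change is measured in each arm, and the changes are then compared. They describe outcomes and set no decision rule.

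Most of this stands, and it limits the point. A reader might infer that the trial will declare the app effective from a before-after change, or that its false-positive rate is 40% to 94%. The documents support neither. No paired test and no single-arm criterion appears anywhere, and the same sentences also name the between-group difference. Those percentages belong to a hypothetical test under assumed inputs.

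The illustration also simplifies. The criteria include underweight, which the background defines by weight for age, whereas the growth outcomes are weight for height and BMI for age. If selection acts through a related measure or a separate screening visit, the rise would generally be smaller.

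The reply does not remove the mismatch. The abstract and the Outcomes section name a basis for the results that the statistical section does not test, and no section says that effectiveness rests on the between-group comparison alone. This is something the article states, not a detail left to an analysis plan.

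**Conclusion.** The point holds as a defect of wording with a real risk of misreading. Within-group change is an unranked co-basis of the results in a trial where growth z-scores can rise in both arms for reasons unrelated to the app. For the mothers' scores the same caution applies through usual care, time and retesting only.

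Under the stated assumptions, a within-arm test, if someone ran one, would be significant in about 94% to 40% of trials with no effect (25% to 100% across all the cut-offs and population means tried). The planned type of between-arm test stays near 5%. The direction does not depend on the exact inputs; the percentages do, and they should be quoted as an illustration, not as properties of this plan.

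**What to change.** 1. In the abstract (Methods) and Outcomes {12}, state that effectiveness is judged solely on the between-group difference at 3 months.
2. In Statistical methods {20a}, make adjustment for the baseline value of the outcome standard instead of optional. An arm that starts lower by chance is expected to regress more, and adjustment deals with that.
3. Report within-group changes as descriptive only, for example as means with confidence intervals, without p-values or claims of effect.

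The cost is wording. Baseline and 3-month values are already to be collected, so no participants, visits or data are added. The change should be dated before the data are analysed by arm.

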**Discussion:**

Due to their widespread availability throughout society, smartphones can be used to deliver educational content on a large scale at a low cost. In addition, they can provide novel ways for patients to receive support. Hence, it is essential to conduct research studies on these types of interventions. *MyKid’sNutrition* application offers dietary solutions for such nutritional problems as underweight, loss of appetite, and malnutrition in children. Meanwhile, it provides detailed instructions on how to interact with the child.

**Trial registration:**

IRCT.ir IRCT20140907019082N11. Registered on February 19, 2022.

**Supplementary Information:**

The online version contains supplementary material available at 10.1186/s13063-023-07503-w.

## Introduction

### Background and rationale {6a}

In developing countries, childhood malnutrition continues to be a significant public health and development issue, and inequities in malnutrition persist [1]. Studies demonstrated that undernutrition during childhood has considerable economic consequences regarding children’s health and development, including restricted growth, diminished intelligence, weak cognitive development, and reduced productivity when they become adults [2, 3]. Numerous diseases are associated with malnutrition on a global scale, and undernutrition is responsible for about half of the annual deaths of children under 5 worldwide. In 2020, the World Health Organization (WHO) estimated that 149 million children under 5 were stunted, and 45 million were wasted [4].

Three commonly known indicators of a child’s nutritional state are stunting (low height for age), wasting (low weight for height), and being underweight (low weight for age). While underweight is a compound index encompassing acute and chronic malnutrition, stunting and wasting indicate chronic and acute malnutrition, respectively. However, different types of malnutrition can develop concomitantly in children [5]. Primary indicators of undernutrition-related malnutrition in cases where only one data point is available for diagnosis are as follows: weight for height or body mass index (BMI) for age *z*-scores of − 1 to − 1.9 corresponds to mild malnutrition, − 2 to − 2.9 to moderate malnutrition, and below − 3 indicates severe malnutrition [6]. In addition to food security, the poor nutritional status of a child can also be attributed to access to health services, poor feeding practices in a community, nutritional knowledge and awareness, and quantity and frequency of the consumed food [7, 8].

Positive associations between maternal nutrition knowledge and child nutritional outcomes are well documented for young children. As a proven factor, mothers’ nutritional knowledge significantly affects children’s nutritional status regardless of the family’s income level [9]. Additionally, parents’ knowledge and awareness about children’s nutrition is a more potent risk factor for child malnutrition than the availability of health centers [10]. The low health literacy of mothers causes them to have a poor understanding of children’s health problems and limits their interaction with the healthcare system [11]. Also, it seems that mothers with low health literacy do not clearly understand their children’s nutrition and malnutrition status and, therefore, cannot meet their children’s nutritional needs [12].

Meanwhile, one critical factor impacting people’s access to medical centers in developing countries is the distance of families to medical centers [13]. As a result, some patients may not be able to receive continuous health services due to the distance to the medical center or high transportation costs [14]. Also, it is imperative to note that increasing the distance and time to reach health centers is related to increasing malnutrition [15]. Health and treatment services can now be provided anywhere in the world through information and communication technology and are no longer limited by location. Technology has played an important role in improving health delivery systems, especially in disease control, diagnosis, and patient management. Technology can also be utilized to provide continuous education to patients [14]. In the past decade, smartphone ownership has surged, reaching at least half of the world’s population [16]; hence, smartphones could be used to enhance nutritional knowledge [17].

Smartphone-based technologies have the potential to significantly reduce costs along with providing better results [18]. Parents’ participation in child nutrition interventions can be more effective by using mobile apps to educate them about nutrition [19, 20]. The availability of mobile applications on nutrition education allows patients to follow healthy nutritional interventions even long after completing the treatment. Correspondingly, they reduce the rate of returning from the intervention program and the recurrence of health problems, thus helping to maintain healthy behavior in the long term [21].

A randomized controlled trial (RCT) protocol for *MyKid’sNutrition* is presented in this report, including information on the study’s intervention, design, procedures, and outcome measures. The intervention aims to elevate positive changes in maternal feeding practices and preschool children’s nutritional status by delivering educational content via an app.

### Objectives {7}

In this RCT, the primary objective is to investigate the effectiveness of *MyKid’sNutrition* app on children’s nutritional status and maternal nutritional knowledge, attitude, and practices.

### Trial design {8}

We designed a two-arm RCT to evaluate the efficacy of the *MyKid’sNutrition* app. Following a baseline evaluation, children and their mothers will be randomly allocated to either the experimental group, *MyKid’sNutrition* app in addition to treatment as usual (TAU), or TAU alone as the control group. The patient allocation ratio will be 1:1. Figure 1 represents the *MyKid’sNutrition* RCT flowchart.

**Fig. 1 Fig1:**
[figure not shown]
Flow chart of *MyKid’sNutrition* RCT study

## Methods

### Participants, interventions, and outcomes

#### Study setting {9}

*MyKid’sNutrition* trial will be conducted in Isfahan, Iran. The subjects will be recruited from the pediatric outpatient clinics according to the study’s inclusion criteria.

#### Eligibility criteria {10}

The inclusion criteria will be as follows: children aged 2–6 years at baseline; mothers’ willingness to participate in the study and signing a written consent form; having a smartphone and willingness to use a smartphone application; mothers’ reading and writing skills; and confirmed malnutrition and underweight using growth charts.

There will be two exclusion criteria as follows: subjects suffering from a specific disease that can affect the results and those reluctant to continue participation in the study.

#### Who will take informed consent? {26a}

After the clinical team’s initial assessment, the eligible individuals will receive oral information along with an informational flyer about the study. After describing the research aims to participants and reminding that their participation is voluntary, the participants will sign written informed consent.

#### Additional consent provisions for collection and use of participant data and biological specimens {26b}

The consent form will inquire whether participants consent to the use of their data in the event of withdrawal from the trial or share relevant data with people from the universities taking part in the research or from regulatory authorities, where relevant. This trial will not involve collecting biological specimens for storage.

### Interventions

#### Explanation for the choice of comparators {6b}

This trial will evaluate the effect of *MyKid’sNutrition* mobile application on mothers’ nutritional knowledge and status of preschool children. The control group will receive standard care, which is treatment as usual.

#### Intervention description {11a}

After recruitment into the study, the subjects will be randomized into two separate arms. The participants in the intervention group will receive *MyKid’sNutrition* application, which will provide educational contents on children’s nutrition and weight status. The duration of the intervention will be three months in total. Both groups will receive standard care, which consists of treatment as usual for undernutrition.

### Development of the *MyKid’sNutrition* application

To deliver all the educational content, we designed and developed an application in Persian, the *MyKid’sNutrition* app, which can be installed on a mobile device or accessed via a web browser. The app includes contents of children’s interactive growth charts, textual and multimedia materials on healthy eating education, and contents specific for improving underweight children’s nutritional status.

All participants will have access to the *MyKid’sNutrition* app for free. While designing the application, we attempted to make it an attractive and user-friendly platform. *MyKid’sNutrition* app has five main screens. On the application’s home page, random contents from all available categories will be displayed with attractive and practical titles about improving children’s nutrition. On the user’s profile page, all mothers will be able to see their children’s information (such as name, date of birth, and gender) and edit it if needed. Also, in this section, the participants will be able to view and edit the application’s history of height and weight records. It will also have features like adding a new child profile, cloud data backup and restore, and contact technical support. On the add measurements page, the participants will be able to enter height and weight of the child to display them on the growth charts. In this section, the users will be able to input the weight recorded in the child’s past and see the child’s growth pattern. The topics page will list contents in four categories: (1) children’s healthy eating, (2) underweight children, (3) children’s loss of appetite, and (4) assessing child growth. Finally, different growth charts will be available on the growth charts page, and the child’s growth patterns will be shown based on the weights entered. Figure 2 depicts the app’s features and user interface.

